## Abstract

**Background:**

New technologies have recently been used for monitoring signs and symptoms of mental health illnesses and particularly have been tested to improve the outcomes in bipolar disorders. Web-based psychoeducational programs for bipolar disorders have also been implemented, yet to our knowledge, none of them have integrated both approaches in one single intervention. The aim of this project is to develop and validate a smartphone application to monitor symptoms and signs and empower the self-management of bipolar disorder, offering customized embedded psychoeducation contents, in order to identify early symptoms and prevent relapses and hospitalizations.

**Methods/design:**

The project will be carried out in three complementary phases, which will include a feasibility study (first phase), a qualitative study (second phase) and a randomized controlled trial (third phase) comparing the smartphone application (SIMPLe) on top of treatment as usual with treatment as usual alone. During the first phase, feasibility and satisfaction will be assessed with the application usage log data and with an electronic survey. Focus groups will be conducted and technical improvements will be incorporated at the second phase. Finally, at the third phase, survival analysis with multivariate data analysis will be performed and relationships between socio-demographic, clinical variables and assessments scores with relapses in each group will be explored.

**Discussion:**

This project could result in a highly available, user-friendly and not costly monitoring and psychoeducational intervention that could improve the outcome of people suffering from bipolar disorders in a practical and secure way.

**Trial registration:**

Clinical Trials.gov: NCT02258711 (October 2014).

## Background

Bipolar disorder is a frequent condition in the general population with a high morbimortality [1]. It is characterized by dysfunctional episodic fluctuations between different mood phases ranging from depression to manic episodes with patients presenting frequent interepisodic subsyndromal symptoms. Frequently, people with this condition have a lack of insight about their diagnosis and symptoms, especially regarding manic phases, which leads to poor prognosis [2,3].

Besides the pharmacological treatment, adjunctive psychological interventions have shown to improve the long-term outcome of the disorder [4], although, taking into account the limited resources currently available, their extended implementation is still difficult and costly [5].

Among psychotherapeutic interventions, psychoeducational programs have proven to be cost-effective in helping patients recognize early signs or symptoms and adopt behavioral measures to prevent full-blown episodes which are frequently associated with a high morbidity and more hospital admissions [6,7]. Accordingly, there is an increased need to make this intervention more widely available, without compromising its quality [4].

On the other hand, the wide use and availability of new technologies such as the Internet have been successfully adopted in mental health contexts. Using these technologies in patient’s assessments and interventions have proved their efficacy and reliability as well as their good acceptability from the patient’s perspective [8,9]. The potential improvement in accessibility to healthcare in patients with disabilities or patients living in rural or other remote areas (i.e. telemental health), as well as the lower costs when compared to conventional interventions, makes them an attractive complement to standard treatment [10-13].

Furthermore, the progressively reduced costs and consequent widespread accessibility to mobile phones with internet connection (smartphones) opens an unlimited number of opportunities to the mental health field. In industrialized countries, these devices have become a very popular way of interacting with each other and with the environment. As an example, in Spain, a recent study of the National Institute of Statistics revealed that almost 70% of the population have internet access and in the majority, through a mobile device [14]. This is a growing phenomenon and includes developing countries as well. According to eMarketer Inc., a company which studies technology market trends, by 2017 one-third of all the population around the globe will be using a smartphone [15].

In addition, the constant improvement of portability and benefits of mobile devices allows the quick and continuous collection of relevant users’ information at a low-cost. Data on subject’s activity and interests, through embedded sensors and mobile usage patterns respectively, are collected and complemented with information from other digital services such as social networks, e-mails and internet search patterns. All this information that has been denominated “big data” are integrated, analyzed by data mining and results are used to determine individual user behavior and interests patterns by predictive analytics, which now are commonly used for commercial purposes [16]. Accordingly, there is an increasing interest in medicine and especially in mental health to explore the possibilities and potential applications of this underutilized data [17-20].

The potential of the great amount of data collected by the patient’s smartphones, its analysis and potential applications in treatment interventions are leading the way to the (so-called) “Personalized Medicine” era. Given the diverse types of presentations, course and response to treatments in mental disorders, including new technologies has long been promoted as the obligatory next step in different medical disciplines, and especially in psychiatry [21-24]. However, one major concern about this approach is the potential threats to patient’s privacy and consequent utilization of this data with others intends, if it is transmitted, processed or stored insecurely [25,26].

Several projects have tested the benefits of these new technologies for the treatment of bipolar and psychotic disorders using either online monitoring of signs and symptoms [27,28] or web-based psychoeducational programs [29-32], yet to our knowledge, none of them have integrated both approaches in one single intervention.

The current technology available makes technically easier to integrate into patient’s life a comfortable, simple, time-unconstrained, user-friendly, economical and non-invasive method of registering and monitoring relevant signs and symptoms and provide continuous self-management psychoeducational contents tailored to the specific needs of each individual on the basis of these data registered on their own smartphones [33]. Additionally, this approach could contribute to better understand the pathoetiology as well as prodromal behavior patterns prior to a relapse in bipolar disorders, integrating objective and subjective data with other clinical correlates [17].

We hypothesized that, combining a signs and symptoms monitoring system with continuous feeds of tailored psychoeducational in a single smartphone application as an adjunctive intervention to usual treatment, would add efficacy in preventing relapses, suicide attempts and health resources consumption in bipolar patients improving their overall prognosis.

The aim of this study is to develop and clinically validate a smartphone application to monitor symptoms and signs in bipolar patients, offering customized embedded psychoeducation contents and empower the self-management of their disorder in order to prevent relapses and hospitalizations. Secondary objectives are to explore other clinical benefits among the smartphone application users such as improvements in biological rhythms, manic/hypomanic and depressive symptoms, quality of life, suicide attempts and pharmacological treatment adherence.

## Methods and design

Given the incipient nature of the field, we adopted an eclectic approach considering and combining multiple guidelines and recommendations about developing internet and mobile interventions for mental health [34-36]. In order to consider technical aspects and an adequate clinical validation while including patients preferences and safety along the process, it was determined that the project will be carried out in three complementary phases, which will include two clinical studies. The studies will follow the Consolidated Standards of Reporting Trials (CONSORT) guidelines to describe, report and publish the results [37] (Figure 1).

**Figure 1 Fig1:**
[figure not shown]
**The figure shows a flowchart of the SIMPLe project phases (left) and their expected duration (right).** *Current status of the study. TAU = Treatment as usual.

### Application development

During one year (May 2013 to May 2014) a collaborative team of specialists in bipolar disorder (psychiatrists and psychologists from the Bipolar Disorders Program of the Hospital Clínic of Barcelona) and software engineers as well as graphical designers held periodical meetings in order to determine the design of an online tool to monitor and register signs and symptoms of bipolar disorder and offer personalized psychoeducation contents. At the end of this process, the team resolved to develop a smartphone application with the following characteristics: user-friendly, non-stigmatizing and sensitive enough to detect mood changes in order to give customized psychoeducational feedback based on an existing psychoeducation group treatment manual [38], which has been previously tested by the Barcelona Bipolar Disorders Program [6].

Several evidence-based methods for self-mood assessment were considered taking into account the aims of the project. We chose 5 daily key questions balancing sensitivity and privacy, which are intended to be answered in a few seconds with the aid of an animated graphical interface (i.e. mood, energy, sleep time, irritability and medication adherence). If a relevant mood change is detected by means of an algorithm that takes into consideration the previous week mean score of the daily test, the user is requested to answer a more comprehensive second test based on the DSM-5 [39] criteria for mania, hypomania or depression, along with some extra questions regarding substance use and suicide risk. If the patient gives an affirmative answer to the question that explores suicidal ideation, an automatic e-mail message is sent to the mental healthcare team and in addition, an immediate call to emergency services is offered. Otherwise, if the subject is stable during their daily assessments, this DSM5 based test is requested to be answered only once a week.

Furthermore, the application will give feedback with a graphic showing daily mood changes and the user will be able to review the results of previous tests. Personalized daily psychoeducative messages will be sent based on the patient’s answers. The user will be able to customize the best time of the day to answer the test and to receive the psychoeducative messages at his or her convenience (Figure 2).

**Figure 2 Fig2:**
[figure not shown]
**The chart shows the way in which the application SIMPLe 1.0 gives psychoeducative messages based on the answers of daily and weekly tests.**

Simultaneously, a web-based interface will be developed to allow the mental healthcare team to follow and monitor patient status.

The collaborative team decided that it was necessary a first study to determine the acceptability and validity of an application based solely on subjective information (SIMPLE 1.0), prior to the addition of objective monitoring data modules (SIMPLE 2.0) for three reasons: 1. In order to give patients active participation in the development of the application through focus groups and satisfaction surveys based on the experience with the first SIMPLE version and adapt the application to their preferences; 2. To test data safety and confidentiality issues with a smaller sample; 3. To adjust possible mood sensitivity issues with the daily and weekly questionnaires which were not previously validated in a real-world clinical setting (Figure 3).

**Figure 3 Fig3:**
[figure not shown]
**Screenshots of SIMPLe 1.0 running in an Android Smartphone.**

### Study design and phases

The studies to evaluate the smartphone application will be carried out in three different but complementary phases as detailed below.**First phase:** A three months lasting feasibility study will be conducted in order to evaluate the use, reliability and patient satisfaction with symptom monitoring (subjective information). Patients under usual treatment will use a smartphone with the SIMPLe version 1.0 application installed. The intervention will be consecutively offered to 30 stable adults (>18 years) fulfilling the inclusion criteria described below. An informed consent will be handled and explained and must be signed in order to participate. Sociodemographic data and standardized clinical as well as functional assessments will be administered at baseline and monthly for three months. Assessments will include present manic symptoms using the Young Mania Rating Scale (YMRS) [40,41], depressive symptoms using the Hamilton depression Rating Scale (HDRS) [42,43], biological rhythms using the biological rhythms interview of assessment in neuropsychiatry (BRIAN) [44,45] and treatment adherence using the Morisky Green 8-item test [46]. A smartphone device with the SIMPLe 1.0 application pre-installed, will be given to the participants for free during the study with the mandatory condition that it has to be their main mobile-phone during the next 3 months. In the case the patient accepts to participate but doesn’t want to switch from his/her current smartphone, he/she will be offered the possibility to download the SIMPLe 1.0 application from the Application Store and a username and password will be given. The subject will receive a customizable automatic reminder in their smartphone to answer both daily and weekly questionnaires based on DSM-5 criteria for a manic, hypomanic, mixed or depressive episodes. The data obtained will be registered online. During this period of time, the subjects will receive daily customized psychoeducative messages based on the information collected by the application using an algorithm designed by our team. Feasibility and satisfaction will be assessed with the application usage log data and with an electronic survey. Reliability will be analyzed comparing the clinical assessments made by a psychiatrist and the information about mood state collected by the application**Second phase:** Three different focus groups (patients, psychiatrists and psychologists, software engineers and graphical designers) of 3 sessions each will be held to discuss the experience with the SIMPLE 1.0 app and recollect suggestions and bugs. Additionally, individual personal interviews with each SIMPLE 1.0 user will also collect qualitative information about the application and suggestions. Taking into consideration the information collected from participants in the first phase, the application will be adapted and improved with the addition of objective information (signs) monitoring modules using mobile usage parameters and the built-in actimetry sensors.**Third phase:** A six months randomized controlled trial with an intervention and a control arm including 74 patients each. An initial evaluation in both groups will be carried out recollecting sociodemographic data and using standardized clinical as well as functional assessments. This evaluation will be repeated at three, six and twelve months from baseline. The assessments will include present manic symptoms using the Young Mania Rating Scale (YMRS), depressive symptoms using the Hamilton depression Rating Scale (HDRS), functional impairment using the Functioning assessment short test (FAST) [47], biological rhythms using the biological rhythms interview of assessment in neuropsychiatry (BRIAN), quality of life measured by World Health Organization quality of life assessment (WHOQOL-BREF) [48] and treatment adherence using the Morisky Green 8-item test. During the follow-up the number of relapses, inpatient admissions, outpatient consultations, emergency rooms consultations and suicide attempts will be registered.**Intervention arm (SIMPLe 2.0 + TAU):** The experimental group will use the application SIMPLe 2.0 and will keep receiving their usual pharmacological treatment. A smartphone device with the SIMPLe 2.0 application pre-installed, will be given to the participants for free during the study with the mandatory condition that it has to be their main mobile-phone during the next 3 months. In the case the patient accepts to participate but does not want to switch from their current smartphone, they will be offered the possibility to download the SIMPLe 2.0 application from the Application Store and a username and password will be assigned. The self-mood assessments will adopt a similar approach to the SIMPLe 1.0 app. Additionally this information will be complemented with automatically recorded patients activity data which will include smartphone usage, telephone calls made (number of independent calls and total time), social network apps usage, and physical activity measured by the built-in actimeter. Patients will receive daily psychoeducative messages based on the data recollected by the application. Relapse risk will be calculated using an algorithm including both subjective and objective data. The clinical team will be contacted with an e-mail if there is moderate or high risk for an oncoming episode and the patient will be offered the outpatient or emergency for assistance.**Treatment as usual arm (TAU):** The treatment as usual (TAU) group will be followed-up with their standard treatment following the Barcelona Bipolar Disorders Program protocol [49].

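### The main-phone rule for supplied SIMPLe 2.0 handsets lasts 3 months in a six-month trial, so the passive data behind the relapse alerts may be incomplete after month 3

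*Protocol article*

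**What the plan says.** All the key text is in the protocol article, Study design and phases.

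- The third phase is "A six months randomized controlled trial with an intervention and a control arm including 74 patients each". Evaluations are repeated at three, six and twelve months.
- In its intervention arm, the rule for the free handset with SIMPLe 2.0 reads: "has to be their main mobile-phone during the next 3 months. In the case the patient accepts to participate but does not want". What follows concerns patients who prefer to keep the phone they have, and gives them an alternative: "they will be offered the possibility to download the SIMPLe 2.0 application from the Application Store and a username and password will be assigned".
- Nearly the same sentence appears in the first phase: "A smartphone device with the SIMPLe 1.0 application pre-installed, will be given to the participants for free during the study with the mandatory condition". Its condition is likewise use as the main phone for three months, and that phase is itself three months long: "A three months lasting feasibility study will be conducted".
- SIMPLe 2.0 adds "automatically recorded patients activity data which will include smartphone usage, telephone calls made", social-network app use and activity from the built-in sensor. On their use, the text states: "Relapse risk will be calculated using an algorithm including both subjective and objective data". It then adds: "The clinical team will be contacted with an e-mail if there is moderate or high risk for an oncoming episode".

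No section extends the main-phone condition beyond three months or says what happens to phone use afterwards. Nor does any section state outright how long SIMPLe 2.0 is to be used.

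**The concern.** The three-month limit is a definite figure attached to a mandatory rule, and it does not fit the trial length given under the same heading. It is therefore not a detail left to a fuller document.

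The mismatch matters more here than it would have in the first phase. Application development describes SIMPLe 1.0 as resting on subjective information only, so a patient could answer its questions on any handset. The passive data in SIMPLe 2.0 describe the patient only if they come from the phone that the patient actually carries. A handset that has become a second phone records fewer calls, less use and less movement. What is at stake is how fully the component that sets SIMPLe 2.0 apart is delivered during the later part of the trial.

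**Working it through.** **1. The plan's own sample size, to settle whether it is affected.** Inputs from Power and sample calculation are alpha 0.05, power 0.8, difference 0.5 and drop-out 15%. The two-sided test comes from Statistical analysis. Reading 0.5 as a standardized difference is an assumption.

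- Normal approximation: n = 2 × (1.96 + 0.8416)² / 0.5² = 62.8, so 63 per arm. The t-test version gives 64.
- Drop-out by division: 63/0.85 gives 75 and 64/0.85 gives 76.
- Drop-out by multiplication: 63 × 1.15 gives 73 and 64 × 1.15 gives 74.

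The stated 74 lies within 2 patients of all four results. It does not depend on the phone rule.

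**2. The two clauses side by side.**

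| | First phase | Third phase, intervention arm |
|---|---|---|
| Length of phase | 3 months | 6 months, with a last visit at month 12 |
| Main-phone rule | 3 months | 3 months |
| Share of phase covered | 3/3 = 100% | 3/6 = 50% |
| Passive sensing | no | yes |

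The version number was updated between the two sentences and the duration was not. Carry-over is an inference, but it fits the wording.

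**3. Which period is the right denominator?** The six-month figure is the stated trial length. Inclusion criterion 6 asks for a data plan for 12 months for using the application. The selection criteria also apply to the three-month first phase, so this supports longer use without settling it. If use is meant to run to month 12, coverage is 3/12 = 25%.

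**4. Exposure that the rule leaves open.** Let s be the share of the 74 intervention patients who take the supplied handset. The documents do not give s, so the whole range is shown, before drop-out.

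- Use to month 6: total 74 × 6 = 444 patient-months; open 74 × 3 × s = 222 × s.
- Use to month 12: total 74 × 12 = 888 patient-months; open 74 × 9 × s = 666 × s.

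| s | Open, use to month 6 | Open, use to month 12 |
|---|---|---|
| 0 | 0 | 0 |
| 0.25 | 55.5 (12.5%) | 166.5 (18.75%) |
| 0.50 | 111 (25%) | 333 (37.5%) |
| 1.00 | 222 (50%) | 666 (75%) |

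These are patient-months without a main-phone rule. They are not patient-months of lost data. Turning them into an effect on relapse would need the share who change phones, the share who reinstall the app, and the contribution of the passive data to the intervention's benefit. The documents give none of these, so no power figure is offered.

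**The case against.** The strongest reply is that the rule is a minimum and that the rest of the text already asks for more. The experimental group is to use SIMPLe 2.0 with no time limit, and the handset is free for the whole study. A reader might infer that a compliant patient may drop the app at month 3. The documents do not support that, because such a patient would be departing from the arm description. What the text does permit is carrying a different phone.

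A reader might also infer that the alerts stop. The mood self-assessments follow the SIMPLe 1.0 approach, and the passive data are described as complementing them. Self-reports, messages and the suicide-risk e-mail can work on any handset on which the patient answers. How the algorithm weights or handles missing passive input is not described, so a claim that it would misjudge risk goes too far.

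Moving to another phone is also partly provided for. Under Randomization, data anonymization and blinding, access goes by an identification number and password and not by device, and a download route exists. That route, however, is offered to patients unwilling to switch phones, and a later change is not addressed. Handover instructions may well sit in a fuller protocol, so their absence here counts for little.

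These replies narrow the consequence. They do not remove the mismatch between a three-month rule and a six-month trial.

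**Conclusion.** The point holds as a minor one. The duration in the intervention-arm clause does not fit the design. After month 3, patients on a supplied handset may carry another phone within the rules, and the passive input to the risk algorithm and clinician e-mails may then be incomplete. Patients using their own phone are outside the issue.

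The firm figure is coverage of 3 of 6 trial months. The exposure left open runs from none to half of the six-month total, depending on an unknown s. Taking six months as the period of app use is itself an inference from the trial length.

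A reader might go on to infer a biased comparison or a known loss of power. Neither follows. With patients analysed as randomized, incomplete delivery does not bias the comparison of the assigned strategies. It could dilute the contrast in relapse, by an amount that the documents do not allow to be worked out.

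**What to change.** In the intervention-arm text of the third phase, replace the three-month duration of the main-phone condition with the whole period of planned app use, and state that period. It is at least the six months of the trial, and longer if use is meant to continue to month 12. Add one sentence telling any patient who changes phone to install SIMPLe 2.0 on the new one through the existing Application Store and username route. Leave the first-phase clause as it is.

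The cost is one changed phrase and one added sentence, with no added visits and no change in sample size. Patients on a supplied handset are held to the condition for at least three more months. Some may find this unwelcome, but the own-phone option stays open to them.
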